## Abstract

**Introduction::**

There is evidence that caesarean section (CS) is associated with increased risk of childhood obesity, asthma, and coeliac disease. The gut microbiota of CS-born babies differs to those born vaginally, possibly due to reduced exposure to maternal vaginal bacteria during birth. Vaginal seeding is a currently unproven practice intended to reduce such differences, so that the gut microbiota of CS-born babies is similar to that of babies born vaginally. Our pilot study, which uses oral administration as a novel form of vaginal seeding, will assess the degree of maternal strain transfer and overall efficacy of the procedure for establishing normal gut microbiota development.

**Methods and analysis::**

Protocol for a single-blinded, randomized, placebo-controlled pilot study of a previously untested method of vaginal seeding (oral administration) in 30 CS-born babies. A sample of maternal vaginal bacteria is obtained prior to CS, and mixed with 5 ml sterile water to obtain a supernatant. Healthy babies are randomized at 1:1 to receive active treatment (3 ml supernatant) or placebo (3 ml sterile water). A reference group of 15 non-randomized vaginal-born babies are also being recruited. Babies’ stool samples will undergo whole metagenomic shotgun sequencing to identify potential differences in community structure between CS babies receiving active treatment compared to those receiving placebo at age 1 month (primary outcome). Secondary outcomes include differences in overall gut community between CS groups (24 hours, 3 months); similarity of CS-seeded and placebo gut profiles to vaginally-born babies (24 hours, 1 and 3 months); degree of maternal vaginal strain transfer in CS-born babies (24 hours, 1 and 3 months); anthropometry (1 and 3 months) and body composition (3 months).

**Ethics and dissemination::**

Ethics approval by the Northern A Health and Disability Ethics Committee (18/NTA/49). Results will be published in peer-reviewed journals and presented at international conferences.

**Registration::**

Australian New Zealand Clinical Trials Registry (ACTRN12618000339257).

## Introduction

1

### Background and rationale

1.1

Caesarean section (CS) is a surgical intervention intended to reduce risks to the health of women and babies in cases where vaginal birth is considered unsafe. There has been a dramatic worldwide increase in rates of CS; in 1990 fewer than 1 in 10 women gave birth in this manner, whereas by 2014 this figure was closer to 1 in 5.^[1]^ In New Zealand, about 25% of babies are born by CS.^[2]^

A recent meta-analysis of long-term benefits and risks associated with CS reported reduced rates of urinary incontinence and pelvic organ prolapse in women giving birth at term.^[3]^ However, it also highlighted a range of other increased health risks to both mother (e.g., subsequent stillbirth, placenta previa, and placenta accreta) and child (e.g., childhood obesity).^[3]^ Indeed, a 2015 meta-analysis reported a risk ratio of 1.29 for obesity in offspring born by CS, compared to those born vaginally.^[4]^ Since then, a number of other studies have also reported increased risk of obesity in children born by CS,^[5–8]^ although not consistently.^[9]^ Of note, a US study of over 22,000 participants found a 64% increased risk of obesity for those born by CS compared to their vaginal-born siblings.^[10]^ This increased risk may be established early. One study detected accelerated weight gain among infants born by CS as soon as 3 months,^[11]^ while another reported higher mean body mass index (BMI) at 6 months, although this difference was not observed in later childhood.^[12]^ Aside from obesity, there is also inconsistent evidence for an association between birth by CS and increased risk of asthma,^[13–18]^ eczema/atopic dermatitis,^[16,18]^ coeliac disease,^[19–22]^ and type 1 diabetes.^[23–26]^

Altered colonization of the gut microbiota in babies born by CS may partially account for the increased risk of obesity and other health conditions. For many years, the sterility of the womb was accepted as fact.^[27]^ In recent years, evidence has emerged of a placental microbiota,^[28–30]^ although this remains controversial, and even if in existence, its biological significance remains speculative.^[31]^ Birth is an important process for the initial colonization of the gut microbiota. Babies born vaginally are exposed to their mother's vaginal microbes during birth. These microbes are likely to be dominated by species of *Lactobacillus,* key vaginal colonizers,^[32]^ particularly during pregnancy.^[33,34]^ Previous research of 178 mother-baby dyads showed that maternal microbial strains were much more frequently transmitted to the gut microbiota of babies born vaginally during the neonatal period than CS-born babies.^[35]^ Neonates’ stomachs are pH neutral for several hours post-birth due to the amniotic fluid they swallow in utero,^[36]^ thereby enabling survival of bacteria ingested during birth. The early gut microbiota of vaginal-born babies is dominated by species of commensal bacteria such as *Bifidobacterium* and *Bacteroides*,^[35]^ which are associated with improved immune function and reduced inflammation.^[37]^

Babies born by elective CS do not encounter maternal vaginal microbes, while there is conflicting evidence as to whether this is the case for babies born by emergency CS.^[35,38]^ Overall, the early gut microbiota of babies born by CS is dominated by typical hospital and skin colonisers, for example, *Staphylococcus*^[35]^ and *Streptococcus*.^[39]^ In fact, gut colonization by *Bacteroides* has been shown to be delayed up to one year for CS-born babies.^[40,41]^ Interestingly, the gut microbiota of 1-week old CS-born babies has been found to have increased abundance of Firmicutes and decreased abundance of Bacteroidetes compared to vaginal-born babies, although no such differences were seen by 8 or 24 weeks of age.^[42]^*Bifidobacterium* numbers are reduced in the early gut microbiota of children above a healthy weight by 7-years of age,^[43]^ as is also the case in the early gut microbiota of CS-born babies.^[35]^ Therefore, given that dysbiosis (imbalance) of the gut microbiota has been linked to obesity,^[44]^ it is interesting to speculate that impairment in normal microbiota development in CS-born babies is linked to the observed phenotypic changes later in life.

Vaginal seeding (exposure of CS-born babies to maternal vaginal fluids after birth) is a potential mechanism for reducing differences in the gut microbiota of CS-born and vaginal-born babies. In the US, a small pilot study orally and topically swabbed CS-born babies (n = 4) with their mothers’ vaginal microbes shortly after birth.^[45]^ At 1 month of age, these babies had skin, oral, and anal microbiota more similar to those of vaginal-born babies than CS-born babies who were not swabbed.^[45]^ While these findings are encouraging, no baby stool samples were collected so it remains unclear what effect (if any) the seeding had on the babies’ gut microbiota. It is also possible that such swabbing may not be the most optimal method of seeding a baby's gut microbiota; oral administration for example, while previously untested, may be more effective. Further, concerns regarding potential transmission of infectious diseases to neonates has prompted the American College of Obstetricians and Gynecologists to recommend that vaginal seeding only be performed within the context of an approved research protocol until more data regarding safety and benefit are available.^[46]^ Considering the above, it is clear that further research is warranted regarding this promising, but unproven practice.

We describe here the protocol for the ECOBABe (Early COlonization with Bacteria After Birth) pilot study, a prospective, single-blinded, placebo-controlled trial, which will assess the effectiveness of a novel method of vaginal seeding (oral administration) for altering the gut community of CS-born babies. Thirty CS-born babies are randomized to be orally administered active treatment (3 ml vaginal bacteria supernatant) or placebo (3 ml sterile water). The study also includes a reference group of non-randomized vaginal-born babies to enable comparison of microbiota development observed in CS-born babies to that of vaginal-born babies. All eligible babies (randomized CS-born and non-randomized vaginal-born) will be followed up to three months after birth. We have followed the SPIRIT guidelines in the reporting of this protocol.^[47]^

### Objectives

1.2

The objectives of this pilot RCT will be to explore if a previously untested method of vaginal seeding (oral administration) will: i) alter the overall gut community in seeded CS-born babies; and ii) alter the gut profiles of these babies to more closely resemble the gut microbiota of babies born vaginally. If oral administration proves successful, a larger study with longer follow-up will be warranted.

## Methods

2

### Study setting

2.1

The study is assessing the eligibility of pregnant women planning an elective CS or vaginal birth across the entire Auckland region of Aotearoa/New Zealand, where over 20,000 women gave birth in 2017.^[2]^ Maternal vaginal bacteria or placebo is administered to CS-born neonates in hospital theatres shortly after birth. Follow-up of most babies occurs at the Maurice and Agnes Paykel Clinical Research Unit, Liggins Institute, University of Auckland. Some one-month follow-ups occur at a facility closer to, or at, the participant's home (where onsite visit is not practicable).

### Eligibility criteria

2.2

Babies are stratified into one of 2 groups: randomized CS-born or non-randomized vaginal-born. Eligibility assessments occur as a two-step process for each group; the first assessments are antenatal and the second occur at birth. Table 1 outlines exclusion criteria at each step for mothers and babies in the CS group. All pregnant women planning to have an elective CS undergo study-specific antenatal screening no earlier than 10 days before their scheduled CS. This is performed by a member of the research team at our clinical research unit or at a location more convenient for the participant (e.g., local maternity unit or home). All CS group antenatal screening samples are analyzed at Middlemore Hospital Laboratory, Auckland. Table 2 outlines exclusion criteria at each step (antenatal and birth) for those in the vaginal birth reference group.

**Table 1 T1:**
[figure not shown]
Exclusion criteria for mothers and babies in the caesarean section group.

**Table 2 T2:**
[figure not shown]
Exclusion criteria for mothers and babies in the vaginal birth group.

### Interventions

2.3

Eligible babies in the elective CS group are randomized in a 1:1 ratio to receive either active treatment (3 ml vaginal bacteria supernatant) or placebo (3 ml sterile water). A folded 13 × 300 mm sterile gauze with an x-ray strip (Propax, New Zealand) is inserted into the lower vagina of women in the CS group and removed after approximately 30 minutes, as close as possible to their surgery. Women can choose to insert and/or remove the gauze themselves, or have these tasks performed by a clinical member of the research team. Sterile gloves are worn during insertion and removal of the gauze. A counter-signed study swab-count sticker is used to verify the removal of the swab prior to surgery, and added to the woman's clinical notes.

After removal, the gauze is vertically cut into two equal sized pieces using sterile scissors. One piece is kept on ice in a sterile container for transportation back to the Liggins Institute laboratory. The other piece is placed in a sterile syringe with 5 ml of sterile water and mixed to obtain a vaginal bacteria supernatant. Next, 3 ml of this supernatant is transferred to a 3 ml sterile syringe in preparation for oral administration to babies randomized to receive active treatment. The remaining 2 ml of supernatant are transferred to a microcentrifuge tube and stored on ice for transportation back to the laboratory, for later microbiota assessment. If a baby is randomized to receive placebo, only 3 ml of sterile water is placed in the syringe, while the prepared vaginal supernatant is reserved solely for microbiota assessment.

If the attending clinician assesses the newborn as healthy, a member of the research team uses the pre-filled syringe to orally administer either active treatment (3 ml vaginal bacteria supernatant) or placebo (3 ml sterile water). Administration occurs as soon as possible after birth (no later than one hour). Babies in the vaginal-born reference group are not randomized, as no administration of active treatment or placebo occurs in this group.

### Outcomes

2.4

Primary outcome:

Difference in the community structure of the gut microbiota between CS groups at 1 month of age.

Secondary outcomes:

Difference in the overall gut microbiota community between CS groups at 24 hours and 3 months of age.Similarity of CS seeded and placebo gut microbiota profiles to those born vaginally at 24 hours, 1 and 3 months of age.Degree of maternal vaginal bacterial strain transfer in CS-born babies at 24 hours, 1 and 3 months of age.BMI *z*-score at 1 and 3 months of age.Total body fat percentage from whole-body dual-energy absorptiometry (DXA) at 3 months of age.

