#### Sample collection and processing

2.9.7

Baby stool samples are collected by the parents from fresh nappies within the first 24 hours of life, and again at 1 and 3 months of age. Approximately one gram of stool is collected using the scoop attached to the lid of a sterile specimen tube (Sarstedt, Nümbrecht, Germany, Catalogue #SARS80.623). The tubes are prefilled with 5 ml of DNA/RNA Shield^TM^ solution (Zymo Research, Irvine, California, US, Catalogue #R1100) enabling them to be kept stable at room temperature until transfer to the laboratory. Parents are asked to shake the tightly-closed tube to mix the stool with the solution immediately after collection. Parents record the date and time of sample collection on an accompanying collection card. Upon arrival at the laboratory, stool samples are split into 1 ml aliquots and stored at −80°C.

Maternal vaginal microbiota samples (2 ml of vaginal bacteria supernatant and the remaining half of the gauze swab) are collected from all mothers in the CS group just prior to their scheduled CS, and are kept on ice until transfer to −80°C.

Microbial DNA will be extracted using the ZymoBIOMICS^TM^ 96 MagBead DNA kit (Catalogue #D4308) according to the manufacturer's instructions. A blank DNA extraction control consisting of 1 ml of sterile water will be run in parallel for contamination testing. In addition, the ZymoBIOMICS^TM^ microbial community standard (Catalogue #D6300) will serve as an extraction bias control. DNA extracts will be quantified using the Qubit^TM^ dsDNA High Sensitivity Assay kit (Catalogue #Q32851) with a Qubit^TM^ 3.0 fluorometer. Whole metagenome shotgun sequencing will be performed by an independent accredited commercial provider.

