#### Microbial and statistical analyses

2.9.8

Metagenomic sequencing data will be processed with bioBakery workflows using docker images available at http://huttenhower.sph.harvard.edu/biobakery_workflows. Briefly, sequence data quality control, including removal of any human reads, will be conducted using KneadData. Taxonomic and functional profiles of the microbiota will be generated using MetaPhlAn v2.6^[52]^ and HUMAnN2^[53]^ respectively. Strain-level taxonomic profiling will be achieved by SNP haplotype based profiling using StrainPhlAn software.^[54]^ The resulting SNP haplotypes will be used to identify the proportion of shared and unrelated strains between mother-baby pairs, comparing these proportions across treatment groups.

Permutational multivariate analysis of variance (PERMANOVA) will be used to identify any significant differences in the overall microbial community structure between treatment groups. Additionally, Multivariate Association with Linear Models (MaAsLin2) will be used to identify any significant associations between specific microbial taxa and treatment groups. Both taxonomic and functional profiles will be compared. Microbiota stability across time points will be assessed using Bray Curtis dissimilarity. Microbial alpha diversity will be assessed using Shannon's diversity index and gene counts.

Treatment evaluation on clinical outcomes will be performed on the basis of intention to treat, using data collected from all randomized participants. Generalized linear regression models will be used to assess treatment effects, adjusting for sex. Model-adjusted estimates and the difference among the three groups will be calculated and tested. Planned subgroup analysis by sex may be conducted on secondary outcomes to evaluate the consistency of possible treatment effects in males and females. Analyses of non-microbiome data will be performed in SAS v9.4, SPSS v26, and/or Minitab v16. Statistical tests will be two-tailed and significance maintained at 5% level.

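### At 24 hours, differences between seeded and placebo babies in strain sharing and gut community can reflect leftover dose DNA rather than colonisation

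*Protocol article*

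**What the plan says.** **Outcomes (2.4).** The primary outcome is at 1 month: "Difference in the community structure of the gut microbiota between CS groups at 1 month of age". Among the secondary outcomes are "Difference in the overall gut microbiota community between CS groups at 24 hours and 3 months of age" and "Degree of maternal vaginal bacterial strain transfer in CS-born babies at 24 hours, 1 and 3 months of age". Similarity to vaginally born babies is also assessed at 24 hours. Nothing marks 24 hours as a different kind of measurement from the later visits.

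**Interventions (2.3).** Half of the gauze is mixed with 5 ml of sterile water, and the dose for the seeded arm is drawn from it: "Next, 3 ml of this supernatant is transferred to a 3 ml sterile syringe in preparation for oral administration to babies randomized to receive active" (that is, the seeded arm). For the other arm, "If a baby is randomized to receive placebo, only 3 ml of sterile water is placed in the syringe". On timing: "Administration occurs as soon as possible after birth (no later than one hour". The remaining 2 ml of supernatant is kept for microbiota assessment.

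**Sample collection and processing (2.9.7).** Parents collect the first stool during the baby's first 24 hours. The maternal vaginal samples are the 2 ml of leftover supernatant and the other half of the gauze. DNA is extracted from the samples, and "Whole metagenome shotgun sequencing will be performed by an independent accredited commercial provider". The stated controls are an extraction blank and a mock community standard.

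**Microbial and statistical analyses (2.9.8).** Transfer is defined by strain matching: "The resulting SNP haplotypes will be used to identify the proportion of shared and unrelated strains between mother-baby pairs, comparing these proportions across treatment groups". Community structure is compared between treatment groups by PERMANOVA.

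**The concern.** At 24 hours the intervention material can itself be measured as the outcome, and in one arm only. Sequencing extracted DNA cannot distinguish a strain that has established itself in the baby from live cells, dead cells or free DNA of the dose still passing through. Randomisation and blinding of the analysts do not remove the asymmetry, because it follows from the dose.

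This matters because of what the results are meant to show. The Abstract presents the study as judging both strain transfer and the procedure's efficacy for establishing normal gut microbiota development, and Objectives (1.2) makes a larger study depend on oral administration proving successful. A 24-hour difference produced by residual dose could be reported as support for that when nothing had engrafted.

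**Working it through.** The plan gives no figure of its own on this point. The check traces the material through the study and then illustrates the possible effect.

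**Tracing the material**

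1. *Dose (2.3).* Seeded: 3 ml maternal supernatant. Placebo: 3 ml sterile water, so no maternal DNA is given. Both are given within 1 hour of birth.
2. *Stool (2.9.7).* Collected by 24 hours of life, so any stool passed after the dose is less than 24 hours from it. No minimum interval from dose to stool is stated.
3. *Reference (2.3, 2.9.7).* The maternal samples described are the other 2 ml of the same 5 ml supernatant and the other half of the same gauze. Dose DNA present in stool, if sequenced deeply enough, would match them by construction.
4. *Assay (2.9.7).* No step separating live from dead or free DNA is described. The blank addresses reagent contamination and the mock community addresses extraction bias. Neither detects swallowed dose.
5. *Scoring (2.9.8).* Shared-strain proportions are compared across arms, with no separate reading for 24 hours.

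**Illustration 1: strain sharing, no colonisation in either arm**

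Inputs: 15 babies per CS arm (Sample size, 2.6); two-tailed 5% level (2.9.8). Assumptions: each baby is simplified to yes or no for a detected maternal strain; 0 of 15 placebo babies are positive; a fraction q of seeded babies has detectable residual dose.

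With x positives, all in the seeded arm, two-sided Fisher p = 2 × C(15,x) / C(30,x).

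- x = 4: 2 × 1,365 / 27,405 = 0.100
- x = 5: 2 × 3,003 / 142,506 = 0.042

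So five babies are enough. The chance of a significant result is P(X ≥ 5), with X binomial (15, q):

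| q (assumed) | Chance of p < 0.05 |
|---|---|
| 10% | 1% |
| 20% | 16% |
| 30% | 48% |
| 40% | 78% |
| 50% | 94% |

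**Illustration 2: overall community, no colonisation in either arm**

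Both arms were drawn from the same simulated resident community of 40 taxa. Seeded stools were mixed with an assumed share of DNA from a maternal profile dominated by one or two taxa. PERMANOVA on Bray-Curtis distances was applied at 15 v 15 (200 data sets, 199 permutations each).

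| Residual dose share of DNA (assumed) | Rejections at 5% |
|---|---|
| 0 | 5.5% |
| 5% | 36% |
| 10% | 94.5% |
| 20% | 100% |

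These rates depend on the assumed taxa. Both illustrations show what would follow from given amounts of residual dose. Neither estimates how much there is.

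**The case against.** **The outcome is worded as transfer, not engraftment.** This stands. Maternal strains delivered by mouth and recovered in stool are transfer in an ordinary sense, and no sentence in the article equates 24-hour sharing with colonisation. A reader might infer that the plan makes that claim; it does not. The weakness is that nothing separates the two meanings while the Abstract links strain transfer to efficacy.

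**The design already holds the safeguard.** Largely true. The primary outcome is at 1 month, strain transfer is repeated at 1 and 3 months, and stability across time points is assessed. Persistence can be read from samples already planned. That makes the remedy cheap, but it does not alter how the 24-hour arm comparison is set up.

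**Success is not tied to 24 hours.** Correct. Objectives (1.2) names no time point, so a 24-hour result overriding a null 1-month primary is conjecture.

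**The amount of residual dose is unknown.** Also correct. A reader might infer that the dose has reached the first stool and that the 24-hour results must be contaminated. The article gives no transit time, dose load or stool load. Stool passed before the dose arrives contains none of it, and trace DNA may be too sparse for strain calling.

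**This is detail for an analysis plan.** Partly. A caveat on interpretation could sit there. But the article itself fixes the outcome, time point, assay and between-arm comparison, and the point is about that combination.

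**Conclusion.** The point holds in a limited form. The 24-hour seeded-placebo contrasts in strain sharing and community can be positive without colonisation, through a measurement bias that can act in one arm only. This rests on the design and assay as described, not on the illustrative numbers. Its size cannot be determined from the article: in the strain illustration the false-signal rate runs from 1% to 94% as the assumed detection rate goes from 10% to 50%, and it would be nil for stool that predates arrival of the dose.

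The reach is confined to the 24-hour secondary outcomes, including 24-hour similarity to vaginally born babies. It would be wrong to infer that the trial's main result is compromised. The argument does not touch the 1-month primary or the 1- and 3-month strain outcomes, on the reasonable assumption, not stated in the article, that a single 3 ml dose given at birth has cleared by then. This is a worthwhile, inexpensive improvement and not a fatal flaw.

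**What to change.** In 2.4 and 2.9.8:

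- Describe 24-hour strain sharing as a measure of dose delivery or exposure.
- Base the seeded-placebo strain-transfer comparison on maternal strains detected at 1 and 3 months.
- Add, as a persistence measure, the proportion of maternal strains seen at 24 hours that are still present at 1 month.
- State that a 24-hour community difference alone is not taken as evidence that seeding worked.

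**Cost.** Wording, plus one derived summary from stool samples and sequencing already planned. The downside is that the 24-hour result can no longer be claimed as efficacy.
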